## Abstract

Background

Percutaneous nephrolithotomy (PCNL) is considered a standard treatment option for large-size renal stones but is associated with drawbacks such as bleeding and prolonged recovery. Mini-PCNL offers a less invasive alternative, but its efficacy compared to standard PCNL for renal stones larger than 2 cm remains under debate. This study aims to compare the efficacy and safety of standard PCNL versus mini-PCNL for renal stone sizes more than 2 cm.

Methods

This single-centre prospective interventional study will be conducted at Acharya Vinoba Bhave Rural Hospital (AVBRH). The study will include patients 18 to 70 years of age undergoing unilateral PCNL for renal calculi. Patients with renal stones larger than 2 cm will be enrolled. Data on stone-free rate (SFR), operative duration, hospital stay time, surgical site infection, haemoglobin (Hb) drop, need for blood transfusion, and post-surgery fever will be collected and compared between the two procedures. Statistical analysis of data will be performed using descriptive and analytical statistics.

Results

The study aims to enrol a total of 32 patients. Data analysis will be done using IBM SPSS Statistics for Windows, Version 24 (Released 2016; IBM Corp., Armonk, New York).

Conclusion

This study will provide valuable insights into the comparative outcome in terms of efficacy and safety of standard PCNL and mini-PCNL for kidney stones larger than 2 cm.

## Introduction

Percutaneous nephrolithotomy (PCNL), which typically employs a 24-30F tract, is considered the gold standard approach for treating larger renal stones owing to its higher stone-free rate (SFR) [1]. However, it comes with drawbacks and limitations such as intraoperative bleeding, blood clot formation, postoperative pain, and lengthy recovery and hospital stay duration, primarily attributed to its sizable access sheath tract [2]. As a response to these limitations, mini-percutaneous nephrolithotomy (mini-PCNL) emerged, featuring a smaller tract size ranging from 14-22F. The application of mini-PCNL dates back over two decades to the pioneering work of Jackman et al. and Helal et al. in paediatric surgery [3,4]. Despite numerous comparative studies between standard and mini-PCNL, ongoing debate centres on their respective SFR and postoperative complication rates.

Retrograde intrarenal surgery (RIRS), endoscopic combined intrarenal surgery (ECIRS), and extracorporeal shock wave lithotripsy (ESWL) appear less competitive when compared to standard PCNL in the management of kidney stones exceeding 2 cm. This raises the question of whether mini-PCNL, with its minimally invasive nature, could serve as a feasible alternative to standard PCNL in such cases.

## Materials and methods

Study objectives

The primary objective of this study is to compare SFRs between standard PCNL and mini-PCNL. The secondary objectives are to evaluate the operation time for standard PCNL versus mini-PCNL, determine hospitalization duration, assess the incidence of surgical site infections, measure the drop in haemoglobin levels post-procedure, analyze the requirement for blood transfusion, and monitor the occurrence of postoperative fever.

Study design and setting

The study design is a single-centre prospective interventional, randomized controlled study that will be conducted at Acharya Vinoba Bhave Rural Hospital (AVBRH), Wardha district, India.

Statistical analysis

We will utilize descriptive and analytical statistics to analyze the data, presenting it as mean ± standard deviation. Normality will be analyzed using the Shapiro-Wilk test. We will employ either parametric tests (such as the independent sample t-test and paired t-test) or non-parametric tests (such as the Mann-Whitney U test and Wilcoxon signed rank test) as per the distribution of data. Statistical significance will be considered when the p-value is <0.05.

Sample size

The sample size required for this study was calculated using ClinCalc (ClinCalc LLC., Chicago, Illinois) based on the outcomes of previous literature with a mean operating time in minutes. The minimum sample size calculated is 16 in each group. A total of 32 participants will be recruited.

Inclusion criteria

The study will include patients with renal stones >2 cm, patients between 18 and 70 years old, and patients scheduled for unilateral PCNL procedures.

Exclusion criteria

Patients with a body mass index (BMI) of >30 kg/m^2^, patients with active urinary tract infection and coagulopathy, and pregnant females with renal stones will be excluded.

Study method

Ethical clearance will be obtained from the Institutional Ethics Committee of Acharya Vinoba Bhave Rural Hospital (AVBRH). Preoperatively, all the patients will undergo basic investigations such as complete blood counts (CBCs), liver function test (LFT), kidney function test (KFT), PT/INR coagulation profiles, urine routine microscopy and culture, and non-contrast computed tomography (NCCT-KUB) or (CT urography). PCNL will be performed within four weeks of the scan using the standard technique (24Fr) and mini-PCNL (14Fr-20Fr). SFR, surgery time, hospitalization time, haemo­globin drop, haematocrit fall, need for blood transfusion, and post-surgery fever will be compared between the two procedures. Demographic, clinical, and operative data will be collected prospectively. This will include the patient's age, height, gender, weight, BMI, American Society of Anesthesiology (ASA) score, laterality, operation time, and hospital stay duration.

Calyceal puncture will be done using the progressive descent technique in both standard PCNL and mini-PCNL. Stone localization and tract dilatation will be performed under fluoroscopy guidance and size up to 24Fr with sequential metallic Alken dilators. The Amplatz sheath will be used to maintain the tract. The tract dilatation for mini-PCNL will be performed using a dilator size up to 14-16Fr in a single step. We will use a percutaneous universal nephroscope size 24Fr and 20Fr with a 20° angle of view (Richard Wolf GmbH™, Knittlingen, Germany) for standard PCNL and a 12Fr rigid nephroscope (Karl Storz, Tuttling­en, Germany) for mini-PCNL. Stone fragmentation will be achieved using a pneumatic lithoclast or a holmium laser. The intraoperative evaluation of renal stone and fragment clearance, and consequently the completion of the PCNL or mini-PCNL procedure, will be performed using both nephroscopic and fluoroscopic guidance. A nephrostomy tube will be used for temporary drainage as needed in both PCNL and mini-PCNL. Intravenous antibiotics will be given preoperatively to all the patients, which will be continued postoperatively for three days. Analgesics will be given postoperatively to all the patients as and when needed.

Demographic details such as age, weight, height, and gender, as well as intra- and postoperative data, will be meticulously recorded in an MS Excel (Microsoft Corporation, Redmond, Washington) spreadsheet. Complications will be evaluated using the Modified Clavien Dindo grading system for both standard PCNL and mini-PCNL procedures. On the second postoperative day (POD 2), CBC and KFT analyses will be conducted, along with a digital X-ray of the KUB region, to detect any residual stone fragments. The PCN tube will be removed if no clinically significant residual fragments are visible on the X-ray KUB or if they are clinically insignificant. Procedure success will be defined as the absence of residual fragments or the presence of clinically insignificant residual fragments (CIRF), defined as <4 mm non-obstructing, non-infectious, and asymptomatic fragments on the X-ray KUB conducted during the fourth week of postoperative follow-up. Statistical analysis will be done using IBM SPSS Statistics for Windows, Version 24 (Released 2016; IBM Corp., Armonk, New York).

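### Operating time and haemoglobin drop are compared without adjustment, by a test that Shapiro-Wilk selects; pre-specified adjustment for stone size and baseline haemoglobin would be more precise at almost no cost

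*Protocol article*

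**What the plan says.** The Statistical analysis paragraph of the Protocol article (Materials and methods) sets a two-step rule. First, "Normality will be analyzed using the Shapiro-Wilk test". Depending on the result, the analysis takes a t-test, independent or paired, or else switches to "non-parametric tests (such as the Mann-Whitney U test and Wilcoxon signed rank test) as per the distribution of data". The threshold is "Statistical significance will be considered when the p-value is <0.05", with no statement of one or two sides. Data are to be summarised as means with standard deviations. No method that uses a covariate is named anywhere.

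Operating time and haemoglobin drop are both secondary objectives. Operating time is also the only outcome behind the sample size, which was derived "based on the outcomes of previous literature with a mean operating time in minutes". The result of that calculation is given without its inputs: "The minimum sample size calculated is 16 in each group".

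Under Study method, every patient has a full blood count before surgery and another on day 2 after it, and a CT no more than four weeks before the operation. On entry, "The study will include patients with renal stones >2 cm"; no upper limit is given. The listed data run from age and body size to "American Society of Anesthesiology (ASA) score, laterality, operation time, and hospital stay duration". Stone size is not named among them.

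**The concern.** With 16 patients per arm, precision is scarce. Two baseline measurements that plausibly predict the outcomes are taken on everyone before treatment: haemoglobin, and the CT that shows stone size. The entry rule has no ceiling, so stone size may vary widely. The article's Discussion names stone burden as a factor in choosing the approach, and it attributes longer mini-PCNL operations to the need to break stones into smaller pieces. Raw two-sample tests leave that predictable variation in the error term.

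The trial data also decide whether each p-value refers to a difference in means or to a rank comparison. When the rank test is selected, the p-value no longer corresponds to the mean that is reported beside it.

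At stake are wider intervals and lower power than necessary for two secondary outcomes, one of which sized the trial.

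**Working it through.** **The plan's own figure.** The article gives no mean difference, SD, power or sidedness, so 16 per arm cannot be reproduced, only solved backwards. With n = 2(z_α + z_β)²/d², n = 16 results from these standardised differences d:

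| | 80% power | 90% power |
|---|---|---|
| Two-sided 0.05 | 0.99-1.02 | 1.15-1.18 |
| One-sided 0.05 | 0.88-0.91 | 1.04-1.07 |

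I take d = 0.99 (two-sided, 80%) as a working assumption: √(2/16) × (1.960 + 0.842) = 0.99.

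**Operating time.** For the unadjusted t-test, the noncentrality is d√(n/2) = 0.99 × √8 = 2.80 on 30 df, and exact power is 77% (80% by the normal approximation). With one covariate correlated r with the outcome within arms, the noncentrality is d√(n/2) × √(28/29) / √(1−r²) on 29 df. The factor √(28/29) is the price of estimating the slope.

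| r (assumed) | Residual variance 1−r² | Power at d = 0.99 | Power at d = 0.5 |
|---|---|---|---|
| unadjusted | 1.00 | 77% | 28% |
| 0 | 1.00 | 76% | 27% |
| 0.2 | 0.96 | 78% | 28% |
| 0.3 | 0.91 | 80% | 29% |
| 0.5 | 0.75 | 87% | 34% |
| 0.7 | 0.51 | 96% | 47% |

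Break-even is near r = 0.2. At r = 0 the loss is 77.3 − 75.8 = 1.5 points. A simulation with normal errors (6,000 runs) gave 77%, 80%, 86% and 96% for the adjusted model at r = 0, 0.3, 0.5 and 0.7, and its type I error was 5.1-5.5%.

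**Haemoglobin.** Let σ² be the variance at each time (assumed equal) and r the correlation of baseline with day 2. A drop has variance 2σ²(1−r). The ANCOVA residual has σ²(1−r²). The ratio is (1+r)/2:

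| r (assumed) | Ratio | Reduction |
|---|---|---|
| 0.3 | 0.65 | 35% |
| 0.5 | 0.75 | 25% |
| 0.7 | 0.85 | 15% |
| 0.9 | 0.95 | 5% |

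The small-sample cost multiplies the ratio by 29/28. The reductions at r = 0.3 and 0.7 then become 1 − 0.65 × 29/28 = 33% and 1 − 0.85 × 29/28 = 12%. ANCOVA stays ahead until r = 2 × 28/29 − 1 = 0.93.

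**The Shapiro-Wilk rule.** Simulated at 16 per arm (6,000 runs), switching to Mann-Whitney if either arm rejects at 0.05:

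| Distribution | Mann-Whitney chosen (no effect) | Type I error of rule | Power at 0.99 SD: rule / fixed t / fixed Mann-Whitney |
|---|---|---|---|
| Normal | 9% | 4.9% | 77% / 78% / 74% |
| Log-normal, log-SD 0.3 | 36% | 5.5% | 81% / 78% / 80% |
| Log-normal, log-SD 0.5 | 67% | 5.3% | 87% / 79% / 87% |
| Log-normal, log-SD 0.8 | 92% | 5.2% | 96% / 80% / 96% |

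The data therefore choose the test quite often, but this costs neither type I error nor power.

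**The case against.** The strongest reply is that nothing here is an error. An unadjusted comparison is valid in a randomised trial, the named tests are given as examples, and a full analysis plan could add a model. All of that stands. What remains is that the article does state a selection rule, and every test it names is less precise than an available alternative if the covariate is prognostic.

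It is also fair that the gain is assumed: no correlation is documented, and at r = 0.3 operating-time power rises by only about 2 points. The gain is measured against a t-test under roughly normal times. If times are strongly skewed, the selection rule already recovers power through Mann-Whitney, so a model in minutes would gain less over it.

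Four stronger readings are tempting, but the article does not support them:

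- **A stone-size imbalance is likely.** The chance of a difference above 0.5 SD between arms is 2 × [1 − Φ(0.5/√(2/16))] = 2 × [1 − Φ(1.41)] = 16%. The unadjusted standard error already allows for it.
- **The reported quantity is left to chance.** The summary is fixed as mean and SD; only the test switches.
- **Paired tests will be used to compare arms.** The article never assigns them to that. They may describe the fall within patients.
- **Stone size will go unrecorded.** The data list is not exhaustive; it also omits haemoglobin and stone-free status, which must be collected. The omission justifies asking for stone size to be named, and no more.

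**Conclusion.** The point holds as a matter of precision and pre-specification, not validity. The haemoglobin gain is the firmer one: 15-35% less variance for r from 0.7 to 0.3 (12-33% after the small-sample cost), with ANCOVA ahead for any r below about 0.93. It assumes equal variances at the two times. The operating-time gain is less certain: power of 80-96% instead of 77% for r from 0.3 to 0.7, no gain near r = 0.2, and a loss of about 1.5 points at r = 0. It rests on an assumed r, on d = 0.99 solved backwards from 16 per arm, and on roughly normal errors. Both outcomes are secondary, and the primary stone-free rate comparison is untouched. The change is worth making because the possible loss is very small and the data already exist.

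**What to change.** 1. Name stone size (for example, largest diameter) as a recorded baseline variable, taken from the pre-operative CT already done.
2. Pre-specify day 2 haemoglobin by ANCOVA on arm and baseline haemoglobin.
3. Pre-specify operating time by linear regression on arm and stone size, in minutes, to match the scale on which the sample size rests. Give log time as a sensitivity analysis. It estimates a ratio of geometric means, so it should not replace the main model.
4. Name one test for hospital stay in advance, for example Mann-Whitney, and remove the Shapiro-Wilk selection step.
5. State what the paired and signed-rank tests are for.

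The cost is one data column, a few lines of text and one degree of freedom per model, which leaves 32 − 3 = 29. These are standard models that the planned SPSS version can run. No change to recruitment or to any procedure is needed.

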## Conclusions

This study will provide valuable insights into the comparative outcome in terms of efficacy and safety of standard PCNL and mini-PCNL for kidney stone sizes larger than 2 cm, focusing on key outcomes such as SFRs, operation time, hospitalization duration, and postoperative complications. Mini-PCNL, with its smaller tract size, potentially offers significant advantages, including reduced intraoperative bleeding and shorter hospital stays. However, it also presents challenges, such as increased intrarenal pressure and longer operative times. This study will provide a critical analysis of whether mini-PCNL can effectively mitigate the drawbacks of standard PCNL while maintaining high standards of patient care. Conducting this randomized, prospective study at Acharya Vinoba Bhave Rural Hospital will help to clarify the relative benefits and risks of mini-PCNL versus standard PCNL. The findings will contribute to the ongoing discussion about the best practices in the management of large renal stones and assist urologists in making more informed treatment decisions, ultimately enhancing patient outcomes.

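### The 16 patients per group were calculated for operating time, a secondary outcome, so 32 patients is not a size shown to be adequate for the primary comparison of stone-free rates

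*Protocol article*

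**What the plan says.** All the key statements are in the Materials and methods section of the protocol article.

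- **Study objectives:** "The primary objective of this study is to compare SFRs between standard PCNL and mini-PCNL". Operating time comes next, in the other tier: "The secondary objectives are to evaluate the operation time for standard PCNL versus mini-PCNL".
- **Sample size:** the size needed for the study was worked out with an online calculator, "based on the outcomes of previous literature with a mean operating time in minutes. The minimum sample size calculated is 16 in each group", hence 32 in total. No other calculation is given.
- **Statistical analysis:** "Statistical significance will be considered when the p-value is <0.05". No margin for SFR is stated.
- **Study method:** success is binary. It means no residual fragments, or only clinically insignificant ones under 4 mm, on the X-ray in the fourth postoperative week.

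Two other places frame the question. The Introduction asks whether mini-PCNL "could serve as a feasible alternative to standard PCNL in such cases". The Conclusions section promises an analysis of "whether mini-PCNL can effectively mitigate the drawbacks of standard PCNL while maintaining high standards of patient care".

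**The concern.** A sample size supports the comparison it was calculated for. Here the article presents 16 per group as the size the study requires, yet that number comes from a difference in mean minutes, and the primary result will be a difference between two proportions. A number that suffices for a large difference in a continuous measure says nothing about a comparison of proportions, which usually needs many more patients.

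What is at stake is how the primary result will be understood. If the trial has little chance of detecting a moderate loss of stone clearance, a p-value above 0.05 on SFR carries little information. A reader told that 32 patients was the required number could give that p-value more weight than it can bear, particularly when the question put is whether mini-PCNL can stand in for the standard procedure.

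**Working it through.** **Inputs from the article:** 16 per arm, equal allocation, significance at p<0.05, binary SFR.

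**Inputs assumed:** two-sided testing; 80% power where a size is solved for; SFR of 85-95% in the better arm; all 32 patients contributing a result. The article gives no SFR and names no test for it, so two tests are shown: Fisher's exact (conservative) and uncorrected chi-square (more liberal).

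**1. The plan's own figure.** The 16 cannot be reproduced forwards, because the mean difference, SD and power are not in the article. Solving backwards with n = 2(1.96 + 0.842)²/d²:

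- d = sqrt(2 × 7.85/16) = 0.99 SD
- with the t distribution, 1.02 SD

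So 16 per group is what one obtains for a difference in operating time of about one SD at 80% power. The number is possible for that outcome, and nothing here shows it to be miscalculated.

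**2. Power for SFR at 16 per arm.** Exact enumeration: sum the binomial probabilities of all pairs (i, j) of stone-free counts for which the test gives p<0.05.

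| True SFRs | Fisher | Chi-square |
|---|---|---|
| 95% vs 85% | 4% | 10% |
| 90% vs 80% | 5% | 11% |
| 85% vs 75% | 5% | 11% |
| 90% vs 75% | 10% | 20% |
| 90% vs 70% | 17% | 30% |
| 90% vs 60% | 36% | 55% |
| 95% vs 60% | 57% | 74% |

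Starting from 90% in one arm, Fisher's test reaches 80% power only when the other arm is at about 39%.

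In counts: if 15/16 are stone-free in one arm, Fisher's test is significant only at 9/16 or fewer in the other (p = 0.037). With 14/16, it takes 7/16 or fewer (p = 0.023).

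**3. Precision of the SFR difference.** Newcombe's interval combines the Wilson limits (l, u) of each arm. With the same observed proportion p in both arms, the half-width is sqrt((p − l)² + (u − p)²).

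- 15/16 in both: l = 0.717, u = 0.989; half-width sqrt(0.221² + 0.051²) = 0.227
- 14/16 in both: l = 0.640, u = 0.965; half-width sqrt(0.235² + 0.090²) = 0.252
- 12/16 in both: l = 0.505, u = 0.898; half-width sqrt(0.245² + 0.148²) = 0.286

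The expected half-width is therefore about 23 to 29 points. The simple Wald formula, 1.96 × sqrt(2p(1 − p)/16), gives only 17 points at 15/16 and 23 at 14/16. With one or two failures per arm that is too narrow to rely on.

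**4. Size if SFR were the basis.** For 90% vs 80%, with mean proportion 0.85:

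n = [1.96 × sqrt(2 × 0.85 × 0.15) + 0.842 × sqrt(0.09 + 0.16)]² / 0.10² = (0.990 + 0.421)²/0.01 ≈ 199 per arm.

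For 90% vs 70% the same formula gives 62 per arm. Both are before any allowance for loss to follow-up.

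**The case against.** **The equivalence reading is not in the article.** A reader might infer that the sponsor plans to treat a non-significant SFR result as proof of comparable efficacy. No section says so. The stated objective is to compare SFRs. The Introduction sentence is background rationale, and the phrase in the Conclusions section is about patient care in general, not SFR. This objection stands: misreading is a risk created by the framing and the small size, not a stated plan.

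**Non-significance is not certain.** A reader might also infer that p>0.05 is bound to occur whatever the truth. The table above contradicts that for large gaps: 95% vs 60% has 57-74% power. Every power figure also rests on assumed rates and on a test the article does not name. This too stands. The claim is limited to moderate differences, where both tests agree that power is low.

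**Article format.** A condensed article may leave the power, SD and SFR assumptions to a fuller document, as well as the exact analysis of SFR. Their absence is not criticised here. But the article does state which outcome determined the number, and that outcome is not the primary one. A later analysis plan cannot change what the 16 was derived from.

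**The basis is already disclosed.** The article does name operating time as the basis. It does not say what follows from this: that the number does not serve the primary objective.

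**Conclusion.** The concern holds in a limited form. The mismatch is explicit and needs no assumption: SFR is primary, operating time is secondary, and the only sample size calculation uses operating time. Sixteen per group is thus not a size required for the primary comparison.

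The size of the consequence does depend on the assumed SFRs. For a 10-point difference with the better arm at 85-95%, non-significance has a probability of about 89-96%. For 90% vs 70% it is about 70-83%, which is likely but not assured. For observed SFRs of 12/16 to 15/16, equal in both arms, the 95% interval would extend roughly 23 to 29 points either side of zero, so a large loss of stone clearance could not be ruled out. The 16 itself should not be called wrong for operating time, since its inputs are not shown.

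**What to change.** Keep the 32 patients and keep SFR as the primary outcome, and change the text as follows.

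1. In the sample size section, state that 16 per group is the size for operating time only and that the trial is not powered for SFR.
2. Report SFR as a risk difference with a Newcombe (or similar) 95% confidence interval, and give the expected half-width: about 23-29 points for observed SFRs of 15/16 down to 12/16.
3. State in advance that p>=0.05 on SFR will be reported as inconclusive, not as comparable efficacy.

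This costs wording only and no extra patients. The price is a less favourable statement of what the trial can conclude on SFR.

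If the sponsor wants a confirmatory SFR claim, wording will not do. The size would have to be recalculated on SFR with stated rates and power, for example about 199 per arm for 90% vs 80% at 80% power. Making operating time the primary outcome would also remove the mismatch, but it fits the question to the number, and the Discussion already expects mini-PCNL to take longer. It is a debatable trade-off and is not recommended here as the default.

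### The stone-free rate is read on a plain film, but entry does not require a stone that a plain film can show

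*Protocol article*

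**What the plan says.** All places are in the protocol article, Materials and methods, unless stated otherwise.

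- **Study objectives:** "The primary objective of this study is to compare SFRs between standard PCNL and mini-PCNL".
- **Study method, definition of success:** "Procedure success will be defined as the absence of residual fragments or the presence of clinically insignificant residual fragments (CIRF". Fragments count as insignificant if they are below 4 mm and meet three clinical conditions, the last of which is tied to the imaging: "asymptomatic fragments on the X-ray KUB conducted during the fourth week of postoperative follow-up". The text says procedure success rather than SFR, but no other definition is given on which SFR could rest.
- **Study method, second postoperative day:** the check is also a plain film, "along with a digital X-ray of the KUB region, to detect any residual stone fragments". No postoperative CT or ultrasound is named.
- **Study method, preoperative work-up:** every patient has a non-contrast CT or a CT urogram. No baseline plain film is named.
- **Inclusion criteria:** the only condition on the stone is its size: "The study will include patients with renal stones >2 cm".
- **Exclusion criteria:** besides a body mass index limit, "patients with active urinary tract infection and coagulopathy, and pregnant females with renal stones will be excluded". Visibility of the stone on X-ray is not mentioned.
- **Study method, end of surgery:** clearance is checked by nephroscopy and by fluoroscopy.
- **Discussion:** mini-PCNL has to reduce stones to smaller pieces so that they fit through the narrower sheath.

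**The concern.** The trial can enrol a stone that its endpoint test cannot show. A radiolucent stone does not appear on a plain film, so the film will show no residual fragments both when the kidney is clear and when it is not. For these patients the primary outcome is fixed before surgery.

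Two things are at stake. The reported SFR in each arm will be too high as an estimate of clearance. The comparison between arms will also include patients who carry no information about clearance. The second matters in a trial of 32 patients whose size was set on operating time rather than SFR, because nothing was held in reserve for a loss of contrast on the primary outcome.

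**Working it through.** **The plan's own figure.** The article gives 16 per group, based on mean operating time, without means, standard deviation or power, so it cannot be reproduced. Worked backwards at two-sided 5%, 16 per group corresponds to a standardised difference of 0.99 (80% power) or 1.15 (90% power). This point uses the figure only to turn percentages into patients.

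**Inputs.** The article gives 16 per arm, success read on a plain film, and no visibility criterion. It gives no SFR, no radiolucent share and no detection rate. I assume true SFRs of 90% and 75%, and a share f of patients with a stone invisible on plain film of 5% to 20%.

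**Step 1: radiolucent stones.** Let p be the true SFR. Assume that f is the same in both arms, that residual stone is equally likely in radiolucent and opaque cases, and that opaque cases are read correctly. Then

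observed SFR = p + (1 − p)f, and observed difference = (1 − f) × true difference.

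| f | True 90% seen as | True 75% seen as | Difference (points) |
|---|---|---|---|
| 0% | 90.0% | 75.0% | 15.0 |
| 5% | 90.5% | 76.25% | 14.25 |
| 10% | 91.0% | 77.5% | 13.5 |
| 20% | 92.0% | 80.0% | 12.0 |

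The ratio of failure rates does not change: 25/10 = 2.5 without misclassification, and 20/8 = 2.5 at f = 20%. Only the absolute difference shrinks.

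**Step 2: in patients.** The expected number of failures scored as successes per arm is 16 × (1 − p) × f. It runs from 16 × 0.10 × 0.05 = 0.08 to 16 × 0.25 × 0.20 = 0.8. One patient in an arm of 16 weighs 100/16 = 6.25 points, so the loss of 0.75 to 3 points is less than half of one patient's weight.

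**Step 3: power at the top of the range (f = 20%).** Observed rates of 92% and 80% need 131 per arm for 80% power, against 100 per arm for 90% and 75%. With 16 per arm, exact Fisher power falls from 9.7% to 6.3%. Most of the shortfall is therefore present before any misclassification.

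**Step 4: missed residuals in opaque stones.** This is a separate mechanism. If the film detects a share s of the residuals that should count as failure, observed SFR = 1 − s(1 − p). The values of s below are illustrative only.

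- True 90% and 75%, s = 0.8 and 0.4: observed 92% and 90%, a difference of 2 points.
- True 90% and 75%, s = 0.4 and 0.8: observed 96% and 80%, a difference of 16 points.
- True 85% in both arms, s = 0.8 and 0.4: observed 88% and 94%, a false difference of 6 points in favour of the arm with more missed stones.

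So once detection can differ by arm, the direction of the bias is not fixed.

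**The case against.** The strongest case on the other side has five parts.

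1. **The endpoint is explicit and the same for both arms.** It is one film, at one time, with one threshold. Planning surgery on CT and following up on plain film is no contradiction. That stands, and the point does not rest on a contradiction. It rests on the eligibility lists admitting patients for whom the endpoint cannot register failure.
2. **A journal article condenses.** The full protocol might hold a visibility criterion, and if so the radiolucent part of this point falls away. But the article sets out the endpoint imaging and both eligibility lists as stated content, and they do not fit together.
3. **The effect is small.** On the assumed range it is under one patient per arm. That stands and limits the weight of the point.
4. **Nephroscopy is direct vision and does not depend on radio-opacity.** That stands as far as it goes. It may lower the number of residuals left behind, but it decides when surgery ends and does not enter the week-4 outcome.
5. **The film's insensitivity to very small fragments is mostly harmless here.** Fragments under 4 mm that meet the three clinical conditions count as success, so missing them misclassifies nobody. Only missed residuals that should count as failure matter, mainly those of 4 mm or more.

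A reader might infer that the plain film pulls the SFR difference toward zero and so favours a finding of no difference. The article does not support that as a general statement. It needs equal detection in both arms, and the Discussion gives a reason to doubt this: if smaller pieces in the mini-PCNL arm leave residuals that are harder to see, the error would flatter mini-PCNL. A reader might also take a large dilution as given, for example 15 points falling to 7.5 if the film detects half of the residuals. Nothing in the article gives a detection rate, so that figure would be assumption alone.

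**Conclusion.** The point holds in a limited form. As written, a patient with a radiolucent stone is scored a success whatever remains, and SFR is overstated in both arms. If randomisation balances these stones, the absolute SFR difference is multiplied by (1 − f). For an assumed true difference of 15 points and an assumed f of 5% to 20%, 14.25 to 12 points are observed. Balance holds in expectation only, and with 16 per arm a chance imbalance is possible.

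Missed residuals of 4 mm or more in opaque stones are a further source of error. Neither its size nor its direction can be settled from the article. The flaw is worth correcting because it is known in advance and cheap to remove, not because it is large. It does not explain the low power for SFR, which is a separate matter.

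**What to change.** 1. Add one baseline item, completed before randomisation: is the index stone visible on plain film, judged from the scout image of the CT already planned for every patient?
2. Then choose one of two routes. Either add a stone not visible on plain film to the exclusion criteria, or make patients with a visible stone the primary SFR analysis set and report all randomised patients as a sensitivity analysis. The set is defined at baseline, so the randomised comparison within it is preserved.
3. Report the endpoint as KUB-based success, and state that this is the definition of SFR.

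**Cost.** There is no new test. On the assumed range, the analysis route removes 32 × 0.05 = 1.6 to 32 × 0.20 = 6.4 patients from the primary SFR set. The exclusion route means finding about 32/0.95 = 34 to 32/0.80 = 40 otherwise eligible patients to enrol 32, and it narrows the population to which the result applies.

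**Limit.** The change does not cure missed residuals in opaque stones, and the report should say so. A week-4 CT is not part of this recommendation, because it would add a procedure for every patient.
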